**Figure 1. f1:**
[figure not shown]
Study 1 design overview.

The three analytic approaches generate distinct, complementary research questions for the project’s primary aim of algorithm development:
•Research Question 1: Do Relative Amplitude, Intradaily Variability, and/or Interdaily Stability emerge as independent predictors of time to relapse using Cox Survival Analysis?•Research Question 2: Can a Dynamic Bayesian Network Analysis of RAR parameters predict change in BD psychopathology and full-threshold relapses in a sample of individuals with BD I and II?•Research Question 3: Can Hadaeghi’s Complex System Model, trained on statistical, time-frequency, and nonlinear dynamic features from RAR data collected from a cohort of
*n* = 75 participants predict relapse in an unseen subset of
*n* = 25 participants?•Research Question 4: Do the three approaches to analysis (Cox Survival Analysis, Dynamic Bayesian Network Analysis, and Hadaeghi’s Complex System Model) generate convergent findings about relapse risk prediction from RAR?

*Study 2: Exploring replicability of models in a lower-middle income sample; testing molecular rhythmicity correlates of RAR variables.*

Study 2 (India) repeats Study 1’s prospective design amongst interepisode individuals with BD, but with only one 26-week epoch (
Figure 2). Study 2 aims, first, to explore the replicability of Study 1’s models of relapse prediction in an out-of-distribution cohort from a lower-middle income country (LMIC). Secondly, Study 2 will, (i) test the mechanistic prediction that Relative Amplitude will correlate with diurnal amplitudes of gene expression and metabolites in blood, and (ii) test the hypothesis that both Relative Amplitude and diurnal amplitudes of gene expression and metabolites in blood are attenuated in individuals with BD (
*N* = 25) relative to matched healthy controls (
*N* = 25).

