### Work packages

2.2

Three prospective monitoring studies are planned as three work packages. A fourth integrative work package will synthesise mechanistic and modelling findings from Studies 1–3 and develop the theoretically-informed relapse risk algorithm for testing in future independent samples.

*Study 1: Predicting relapse in interepisode BD from rest-activity rhythms*

Study 1 (Australia) provides the primary 18-month dataset on which to conduct Cox Survival Analysis, develop Dynamic Bayesian Network models predicting evolution of symptoms and full-threshold relapse, and to train/test Hadaeghi’s Complex System Model. A total of
*N* = 100 individuals with BD will wear actigraphs for 14 days at the start of each of three consecutive 26-week monitoring epochs (for a total window of 3 × 26 = 78 weeks forecasting, see
Figure 1). In Study 1 (and Study 2), time to relapse will be measured on the retrospective LIFE interview
^
77
^ conducted at 13 and 26 weeks of each epoch. We propose that 26 weeks is a clinically meaningful timeframe for the present interest in course across weeks and months, as it generates translatable information for use in clinical settings (e.g., at initial assessment, or at the transition from inpatient to outpatient management).

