**Figure 3. f3:**
[figure not shown]
Study 3 design overview.

Study 3 has two additional aims related to improved characterisation of associations between RAR signals and short-term mood dynamics. The secondary aim of Study 3 is to examine the effect of baseline episode polarity—that is, whether the acute episode is depressive or manic—on the performance and structure of the predictive model. The analysis of Study 3’s secondary aim will investigate whether polarity moderates model accuracy against the binary outcome of 50% reduction in symptoms at 8 weeks, using 14 days’ actigraphy data. To increase the granularity of the investigation of this state transition, a tertiary aim of Study 3 is to explore temporal patterns in weekly RAR in relation to weekly clinician ratings of mood (MADRS, YMRS) and clinical state (CGI). The process-focus of this exploratory analysis takes advantage of the full 21 days of actigraphy.

Study 3 therefore investigates the prediction of acute treatment response from RAR variables amongst people who are experiencing a severe episode of BD [an important clinical question in its own right,
78]. Participants will be individuals with BD receiving guideline-based care and treatment
^
75
^ for acute manic (
*N* = 15) or bipolar depressive (
*N* = 30) episodes (on an inpatient, outpatient, or hybrid basis). Participants will be patients of Te Whatu Ora-Waitaha Canterbury Mental Health Services.

Three research questions address the development and testing of a state transition model, and its potential moderation by baseline episode polarity.
•Research Question 1: How many additional samples (
*x*) from the
*N* = 45 Study 3 sample are required to retrain the Study 1 complex system model predicting relapse (
*N* = 75) to achieve acceptable prediction accuracy for
*a state transition model* predicting both relapse amongst interepisode patients and response to treatment amongst acutely ill patients?•Research Question 2: Can a complex system model of state transition trained on
*N* = 75 Study 1 samples and
*x* (from Research Question 1) Study 3 samples predict state transition in an unseen data set of
*N* = 25 Study 1 samples and N = (45 –
*x*) samples from Study 3?•Research Question 3: Is episode polarity at baseline in the Study 3 cohort (
*n* = 30 depression versus
*n* = 15 manic) a moderator for the models developed in Research Question 1 and Research Question 2?

*Work Package 4: Integrative Data Synthesis*

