Work Package 4 will develop an integrated relapse-risk algorithm that synthesises findings from the three preceding studies. The aim is to combine insights from statistical survival models, probabilistic network models, and non-linear dynamical models into a unified predictive framework. We will develop the integrated algorithm as a meta-model, using ensemble learning techniques to combine either the most informative features or the predicted probabilities from each of the component models. This approach will allow the algorithm to take advantage of the strengths of different analytical methods—statistical interpretability from survival models, multivariate pattern recognition from network models (and other forms of machine learning), and dynamic stability indicators from non-linear dynamic models. Model weighting, calibration, and validation will be performed using cross-validation and regularised optimisation to maximise generalisability and avoid overfitting. The resulting meta-model will provide individualised, probabilistic estimates of relapse risk, which can be iteratively refined as additional longitudinal data become available.

In addition to developing this ensemble meta-model, WP4 may include exploratory theoretical work aimed at integrating network-based and complex system approaches in the context of relapse prediction [see, e.g.,
79–
82]. Two lines of innovation are of particular interest. First, multi-perturbation Shapley-value analysis (MSA)
^
83
^ has been extended in our group to study temporal causal connectivity in brain and artificial neural networks.
^
84
^
^,^
^
85
^ MSA can be applied here to rank the relative contribution of variables (or network nodes) to relapse prediction for any given predictive or dynamical model. Second, the team has experience with excitable network modelling, which examines how small perturbations can propagate through a dynamic graph to reveal relationships between structural and functional connectivity.
^
86
^
^–^
^
88
^ These methods will be explored if data structure and model performance indicate potential for further mechanistic insight.

A detailed statistical analysis plan specifying the ensemble architecture, validation approach, and any additional exploratory analyses will be finalised and published prior to conducting analyses.

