### Modelling approaches

2.6

As noted above, it is not possible to present a detailed statistical analysis plan until the data to be analysed is clear. Here, we overview data preprocessing plans, present a power analysis for Study 1, and overview the three planned analytic approaches.

*Data preprocessing*

Two categories of missing data will be identified and managed using tailored approaches. For actigraphy data, short and scattered gaps, where the device is worn but a few data points are missing, will be imputed using forward- and backward-fill (FFill/BFill) methods, which are suitable for brief intervals. Longer and continuous gaps, arising from non-wear periods such as device charging or participant non-adherence, will be addressed using a subject-specific model that combines a circadian baseline estimating expected activity at each clock time with a recurrent neural network (RNN) that models short-term deviations from this baseline. A gating mechanism will determine the weighting between these components according to the duration of the gap, giving greater weight to the baseline for longer periods. All imputed data points will be flagged for potential exclusion in sensitivity analyses.

Missingness in clinical data will be handled according to analytic role: participants missing essential outcomes (e.g., relapse status) will be excluded from analyses requiring those outcomes. Clinical predictors and covariates will not be imputed; analyses will use available-case data. Patterns and proportions of missing data will be reported, and sensitivity analyses will assess the robustness of study findings.

*Power Analysis*

Based on the effect size identified by Ferrand et al (see above), a one standard deviation increase in the actigraphy measure increases the risk of relapse by 57% (Hazard Ratio = 1.57). Assuming a sample size of
*N* = 100 participants, initially assuming zero drop-out and then 20% drop-out (
*N* = 80) we used simulation to calculate power estimates based on different Hazard Rate assumptions for a Cox Survival Analysis in Study 1. First, a sample of
*N* = 100 provides 90.6% power to detect a 57% increase in the relative risk of relapse while a sample size of
*N* = 80 provides 75.6% power to detect such an increase. Second, a sample of
*N* = 100 provides 83.0% power to detect a 49% increase in the relative risk of relapse while a sample size of

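### The complex system model is tested on one hold-out of 25 people with about 11 expected relapsers, too few for a usable estimate of accuracy; cross-validation on shared participant-level folds would roughly halve the standard error

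*Protocol article*

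**What the plan says.** All references are to the Protocol article.

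- **Section 2.2, Study 1, Research Question 3.** The complex system model is trained on n = "75 participants predict relapse in an unseen subset of" n = 25. No resampling is mentioned for this question.
- **Section 2.2, Study 3, Research Questions 1 and 2.** The model trained on the 75 is retrained with x acutely ill participants. Research Question 2 then asks whether the 75 plus x "Study 3 samples predict state transition in an unseen data set of" 25 Study 1 participants and the remaining Study 3 participants. The 25 are evidently the same people.
- **Section 2.2, Study 1, opening paragraph.** Study 1 "provides the primary 18-month dataset on which to conduct Cox Survival Analysis, develop Dynamic Bayesian Network models" and train and test the complex system model. Research Questions 1 (Cox) and 2 (network) state no split. Research Question 4 asks whether the three approaches converge.
- **Section 2.6, Power Analysis.** Cox power is worked out on the whole sample. With nobody lost it is put at 90.6% for a hazard ratio of 1.57; the figure allowing for dropout reads "80 provides 75.6% power to detect such an increase". No N is given for the network model.
- **Section 2.2, Work Package 4.** The ensemble is built "using ensemble learning techniques to combine either the most informative features or the predicted probabilities from each of the component models". Weighting, calibration and validation are to use cross-validation, with the details left to a later analysis plan.

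**The concern.** Developing and cross-validating a relapse algorithm is the project's primary aim (section 1.4). For the complex system model, the only Study 1 evidence of out-of-sample performance is the result in 25 people. If that estimate is very imprecise, Research Question 3 may be answered by which 25 people happened to be drawn, and a lucky or unlucky draw carries over into Study 3 Research Question 2. The Discussion (section 3) names the small amount of data for modelling as the most important limitation, and a fixed hold-out makes that worse by removing a quarter of it from training.

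The second issue is comparability. Sections 1.4 and 2.6 plan to compare the models. If one model is scored on 25 unseen people, while the Cox model is fitted to everybody and the network model's split is unspecified, their performance figures do not refer to the same people under the same conditions.

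**Working it through.** **Inputs.** Rate 0.4 episodes per person-year and about 60 relapses expected (section 3); 78 weeks = 1.5 years and N = 100 (section 2.2); 20% dropout scenario (section 2.6); reference AUCs of 0.64 for clinical predictors and 0.82 with actigraphy added (section 1.3). Assumed: constant hazard, 95% two-sided intervals, and the reference AUCs used only as plausible values.

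**1. Reproduce the plan's figure.** 100 × 0.4 × 1.5 = 60 relapses, as stated.

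**2. Relapsers in the hold-out.** The probability of at least one relapse is 1 − exp(−0.4 × 1.5) = 0.451. In 25 people: 25 × 0.451 = 11.3, so about 11 relapsers and 14 others (95% range 6 to 16 relapsers). After 20% dropout: 20 × 0.451 = 9.0.

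**3. Standard error of the AUC (Hanley-McNeil).** With n₁ relapsers and n₂ others,

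SE² = [A(1−A) + (n₁−1)(Q₁−A²) + (n₂−1)(Q₂−A²)] / (n₁n₂), where Q₁ = A/(2−A) and Q₂ = 2A²/(1+A).

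For A = 0.75: Q₁ − A² = 0.0375 and Q₂ − A² = 0.0804.

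- Hold-out, 11 and 14: (0.1875 + 10 × 0.0375 + 13 × 0.0804)/154 = 0.0104, so SE = 0.102.
- All 100, 45 and 55: (0.1875 + 44 × 0.0375 + 54 × 0.0804)/2475 = 0.0025, so SE = 0.050.

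| People scored | Relapsers / others | SE at AUC 0.75 | 95% CI at AUC 0.64 | 95% CI at AUC 0.82 |
|---|---|---|---|---|
| Hold-out, 25 | 11 / 14 | 0.102 | 0.42–0.86 | 0.64–1.00 |
| Hold-out after 20% dropout, 20 | 9 / 11 | 0.114 | 0.39–0.89 | 0.62–1.00 |
| All, out of fold, 100 | 45 / 55 | 0.050 | 0.53–0.75 | 0.73–0.91 |
| All after 20% dropout, 80 | 36 / 44 | 0.056 | 0.52–0.76 | 0.72–0.92 |

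Upper limits are capped at 1. The out-of-fold rows ignore dependence between folds.

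**4. What the hold-out can separate.** Power = Φ[(A₁ − A₀ − 1.96 SE₀)/SE₁] with 11 and 14:

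- 0.82 against a fixed 0.64: (0.18 − 1.96 × 0.114)/0.090 = −0.49, power 31%.
- 0.82 against 0.50: 84%.
- 0.70 against 0.50: 38%.

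**5. If the outcome is labelled per epoch** (section 2.6 speaks of labelling actigraphy epochs). 25 × 3 = 75 epochs, each with relapse probability 1 − exp(−0.4 × 0.5) = 0.181, gives 13.6 positive and 61.4 negative. The SE at 0.75 is √(5.51/835) = 0.081, before allowing for clustering within person. For all 100 people, 300 epochs split 54.4 and 245.6, and the SE is √(21.85/13361) = 0.040. The ratio is again about two.

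**6. The other available unseen set.** Study 2 follows 25 people with bipolar disorder for 26 weeks: 25 × 0.4 × 0.5 = 5 relapses (4.5 people with a first relapse under a constant hazard).

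**The case against.** The strongest reply is that the project calls itself exploratory, states its small numbers openly and regards replication in unseen data as essential. That stands, and it limits the weight of the point. It does not explain why a noisier design should be preferred when a more precise one uses the same data.

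A reader might infer four stronger things that the documents do not support.

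- **That the ensemble weights will be biased because the Cox and network predictions for the 25 are in-sample.** Nothing says so. Work Package 4 promises cross-validation and defers the validation approach to a later plan. Full-sample use is implied for Cox by the power analysis, but not stated for the network model.
- **That no common unseen set exists anywhere.** The 25 Study 2 participants with bipolar disorder are unseen by every Study 1 model, and all three frameworks are examined there. The reservation is size (about 5 relapses) and that the network question is not worded as a replication.
- **That the hold-out cannot tell a useful model from a useless one.** At a true AUC of 0.82 it has about 84% power against 0.50. The weakness shows at 0.70 (38%) and against the clinical-only value (31%).
- **That reuse in Study 3 leaks data.** Those 25 stay outside training. Reuse means only that the second test is no fresh check on the Study 1 part.

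Research Question 4 also asks about convergence, not a ranking, and Research Question 1 is inferential, so a full-sample Cox fit is appropriate there. Labelling by epoch softens the imprecision, but only to a standard error of about 0.08 before clustering.

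**Conclusion.** The point holds for precision, and in a limited form for comparability. With about 11 expected relapsers, the single 25-person hold-out gives a standard error of about 0.10 at an AUC of 0.75. Even an observed AUC of 0.82 would be compatible with the 0.64 quoted for clinical predictors alone. Scoring all participants out of fold roughly halves this standard error, and also uses the quarter of the sample now withheld from training. Separately, the split is stated for one framework only, so Study 1 fixes no common basis for comparing predictive performance. That is a gap to close; it does not demonstrate bias in the ensemble or in any ranking.

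The figures rest on the protocol's 0.4 episodes a year, a constant hazard, one outcome label per person (or per epoch where stated), and the Hanley-McNeil approximation. The gain is somewhat overstated to the extent that out-of-fold predictions are dependent.

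**What to change.** 1. Replace the single 75/25 split in Study 1 Research Question 3 by repeated nested cross-validation on all Study 1 participants, with tuning and feature selection inside the training folds.
2. Assign folds by participant, so that one person's three epochs are never divided between training and test.
3. Use the same outer folds for the predictive performance of the Cox, network and complex system models, and compare them on those predictions with participant-level bootstrap intervals.
4. Pass only out-of-fold predictions to the cross-validated ensemble that Work Package 4 already plans.
5. Refit on all participants for the final algorithm.
6. Reword Study 3 Research Questions 1 and 2 to match, since both rest on the 75/25 division.
7. Keep the full-sample Cox fit for Research Question 1 as the inferential analysis.

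The cost is computing time, the rewording, and the loss of one simple locked hold-out that is easy to explain. No new data are needed and data collection is unaffected. The change can be made in the analysis plan that the protocol describes as forthcoming.

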**Figure 2. f2:**
[figure not shown]
Study 2 design overview.

Three research questions and two hypotheses are therefore set for Study 2:
•Research Question 1: Does the Cox Survival Analysis model derived in Study 1 replicate amongst
*N* = 25 BD participants in an LMIC cohort?•Research Question 2: Does Dynamic Bayesian Network Analysis enable examination of relapse prediction amongst
*N* = 25 BD participants in an LMIC cohort?•Research Question 3: Does Hadaeghi’s Complex System Model of relapse prediction derived in Study 1 replicate amongst
*N* = 25 BD participants in an LMIC cohort?•Hypothesis 1: Amongst the complete sample (
*N* = 50), Relative Amplitude will correlate with the diurnal amplitude of both circadian gene expression and blood metabolites.•Hypothesis 2: Diurnal amplitude of circadian gene expression and blood metabolites, and Relative Amplitude will be attenuated in people with interepisode BD (
*N* = 25) compared to age, gender, and employment-matched healthy controls (
*N* = 25).

*Study 3: Exploring generalisability of the Complex System model of state transition from relapse prediction to treatment response.*

Study 3 contributes to the project’s secondary mechanistic aim by investigating if complex system features found in Study 1 to predict relapse (state transition into an episode) generalise to prediction of treatment response from an acute episode (state transition to recovery). If generalisation is demonstrated, it could be hypothesised that Hadaeghi’s Complex System Model captures generic system instability (as opposed to a relapse-specific process).

The primary aim of Study 3 is therefore to investigate whether the relapse risk algorithm informed by Hadaeghi’s Complex System Model (trained and tested on Study 1 data) can be extended to response to treatment.
^
19
^ The state transition of Study 3 is measured in binary response to treatment. Response to treatment at 8 weeks is operationalised as 50% reduction in MADRS (for those in depressive episode at baseline) or 50% reduction in YMRS (for those in manic episode at baseline). Participants will wear actigraphs for 21 days – for consistency with Study 1 and 2, the first 14 days only will be used in modelling of binary response to treatment.
Figure 3 below summarises the study design for this primary aim.

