### The Tipping Point project

1.4

The Tipping Point project is fundamentally exploratory. Its primary aim is to
*develop and cross-validate an RAR algorithm of relapse risk for BD.* The algorithm could form the basis of a future actigraphy-based early warning device for people living with BD. The project applies three analytic frameworks (see
2.2 and
2.6 below) to develop predictions of BD course from RAR – statistical risk (Cox Survival Analysis), probabilistic network graphs (Dynamic Bayesian Network Analysis) and non-linear dynamic analysis (Hadaeghi’s Complex System Model of BD).

The project’s secondary aim is to contribute to improved mechanistic understanding of SCRD in BD as measured by RAR in this forecasting context. Consistent with the brief literature review above, two types of mechanism warrant investigation. First, to ground the actigraphy signal in circadian biology, RAR parameters will be correlated with circadian gene expression patterns amongst people with BD and a matched control sample. Second, by conceptualising relapse in non-linear dynamic terms as a state transition, we explore whether Hadaeghi’s Complex System Model
^
19
^ applied to prediction of
*relapse* generalises to prediction of an alternative clinically significant state transition, namely,
*response to treatment* for an acute episode.

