*N* = 80 provides 83.8% power to detect a 65% increase in the relative risk of relapse. This suggests that even with a 20% dropout the study is nearly sufficiently powered to detect the expected relative risk of relapse (Hazard Ratio = 1.57) and powered to detect a slightly higher relative risk of relapse (Hazard Ratio = 1.65). Note also that the selected sample sizes of
*N* = 100 people with BD in Study 1, 50 in Study 2 (25 BD, 25 matched controls), and 45 in Study 3 (15 manic and 30 depressed) were pragmatic maxima. Recruitment beyond these pragmatic maxima will continue if resourcing permits.

*Cox Survival Analysis*

Cox Survival Analysis will be employed with Elastic Net
^
97
^ to determine variables to include. Relative Amplitude, Intradaily Variability, Interdaily Stability will be included as predictors in a random effects or frailty model of survival time to relapse (across the three epochs of Study 1 and the single epoch of Study 2). Initial time to first episode analysis: Proportional Hazards (Cox) regression with the five clinical covariates listed above. For the modelling of recurrent episodes a Prentice-Williams-Prentice (PWP) model will be used rather than a frailty model because the PWP is appropriate when only a small number of events is likely.
^
98
^

To model the relationship between the actigraphy signal and time to first episode, a two-stage joint survival model will be used. These models analyse time-to-event outcomes that may be linked to biomarkers that are repeatedly measured. A two-stage joint survival model analyses time-to-event outcomes influenced by a longitudinal, time-varying biomarker by fitting two separate models in sequence: a longitudinal model for the biomarker and a survival model for the event. This is a computationally efficient alternative to fully joint models, which can be very time-consuming to fit. The main drawback is that standard two-stage methods can disregard the uncertainty from the first stage’s estimates when they are used in the second, though advanced methods use techniques like multiple imputation to account for this.
^
99
^

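### Study 2 Hypothesis 1 is stated as a correlation across BD and controls pooled, so the group differences predicted by Hypothesis 2 would contribute to it even without any within-group link

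*Protocol article*

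**What the plan says.** The protocol article sets two hypotheses for Study 2 (section 2.2, Work packages).

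- **Hypothesis 1** is placed in BD and controls together: "Hypothesis 1: Amongst the complete sample" (N = 50), with the prediction that "Relative Amplitude will correlate with the diurnal amplitude of both circadian gene expression and blood metabolites".
- **Hypothesis 2** predicts a group difference in the same direction on the same variables: "Diurnal amplitude of circadian gene expression and blood metabolites, and Relative Amplitude will be attenuated in people with interepisode BD", "compared to age, gender, and employment-matched healthy controls".

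Section 2.6 confirms the sizes as "50 in Study 2 (25 BD, 25 matched controls"). Section 1.4 gives the purpose of the correlation, which is to tie the actigraphy signal to circadian biology, and names the same combined population: "RAR parameters will be correlated with circadian gene expression patterns amongst people with BD and a matched control sample".

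Nowhere does the article adjust this correlation for diagnosis, stratify it, or plan estimates within each group. Matching is on age, gender and employment. Section 2.6 sets out to "present a power analysis for Study 1, and overview the three planned analytic approaches", so no alpha, effect size or power is given for either Study 2 hypothesis.

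**The concern.** When two variables are both lower in one of two pooled groups, they correlate across the pool even if they are unrelated within each group. Hypothesis 2 predicts exactly that pattern. Read plainly, Hypothesis 1 therefore measures a mixture of two things: any coupling between Relative Amplitude and molecular amplitude, and the shared shift between cases and controls. Matching on age, gender and employment does not remove the shift, because diagnosis is the contrast the design creates.

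What is at stake is the first half of the project's secondary aim, the molecular basis of the rest-activity parameters. A positive pooled correlation alone could not separate coupling from case status, or from anything else that goes with it, such as the ongoing medical treatment that section 2.1 requires of clinical participants. Support for Hypotheses 1 and 2 together could then look like two findings when the second largely produces the first.

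**Working it through.** The article states no figure for these hypotheses, so there is none to reproduce. The check asks how large the artefact can be.

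**Inputs from the article:** 25 BD and 25 controls; correlation in all 50; both variables predicted lower in BD.

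**Assumptions:** two-sided 5% test; normal variables with unit within-group SD; zero within-group correlation; standardised BD–control differences d1 (Relative Amplitude) and d2 (molecular amplitude), shown over a range.

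**Step 1: pooled population correlation.** With two equal groups, the group shift adds d1·d2/4 to the covariance and d²/4 to each variance:

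ρ = (d1·d2/4) / √[(1 + d1²/4)(1 + d2²/4)], which for d1 = d2 = d is (d²/4)/(1 + d²/4).

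- d = 0.5: 0.0625/1.0625 = 0.06
- d = 0.8: 0.16/1.16 = 0.14
- d = 1.0: 0.25/1.25 = 0.20
- d = 1.2: 0.36/1.36 = 0.26

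The critical |r| at N = 50 is 0.279.

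**Step 2: false-positive rate.** Simulation of 25 + 25, 20,000 samples per row, same d on both variables:

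| d on both | Pooled ρ | Pooled test rejects | Group-adjusted test rejects |
|---|---|---|---|
| 0.3 | 0.02 | 5.4% | 5.0% |
| 0.5 | 0.06 | 6.7% | 4.9% |
| 0.8 | 0.14 | 16% | 5.2% |
| 1.0 | 0.20 | 29% | 5.0% |
| 1.2 | 0.26 | 48% | 5.1% |

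**Step 3: unequal differences.** The artefact depends on the product d1·d2, so one small difference limits it. The simulation used 40,000 samples per row:

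| d1 | d2 | Pooled ρ | Pooled test rejects |
|---|---|---|---|
| 0.15 | 0.8 | 0.03 | 5.3% |
| 0.25 | 1.0 | 0.06 | about 7% |
| 0.25 | 1.2 | 0.06 | about 7% |

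**Step 4: which d matters here?** The difference that 25 per group detects with 80% power is (1.96 + 0.84)·√(2/25) = 0.79. If Hypothesis 2 is to have a good chance of success on both variables, d must be near 0.8 on both, and there the pooled test's error is about three times nominal.

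**Step 5: cost of adjusting.** For a true within-group correlation of 0.4, Fisher's z gives a power of about 83% for a plain correlation in 50 people, 82% after adjustment for group, and 51% in the 25 BD participants alone.

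**The case against.** Four points can be made on the other side.

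- **The text fixes a sample, not an unadjusted test.** A regression with a group term also uses all 50 people, and the article defers detail to study-level protocols and an analysis plan. This stands in part: adjustment is not excluded, and a reader who infers that the project has committed to an unadjusted test goes beyond the text. But the hypothesis as worded is the pooled correlation, and an analysis that follows it literally has the problem shown.
- **The group differences may be small.** The only figure in the article that links Relative Amplitude to BD is an odds ratio of 1.11 (1.03–1.20) per quintile decrease (section on prediction of course from RAR). Assuming normality and a rare outcome, a quintile score moves about 1.33 per SD, so d ≈ ln 1.11 × 1.33 = 0.14, and ln 1.20 × 1.33 = 0.24 at the upper limit. At such values the inflation is slight. This stands as a limit on size, although that figure concerns lifetime BD and a clinical sample may differ more.
- **Diagnosis may lie downstream of both variables.** Section 1.2 raises low amplitude as a possible endophenotype, and conditioning on a consequence of both variables can itself distort their association. This is a reason to report both estimates. It does not make the pooled estimate sufficient alone as mechanistic evidence.
- **The project is avowedly exploratory.** This bears on severity. These are nevertheless the two stated hypotheses of Study 2, and section 2.2 says they will be tested.

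**Conclusion.** The point holds in a limited form. If Hypothesis 2 is true, the pooled population correlation in Hypothesis 1 is non-zero without any within-group association, so a positive result is not separate evidence of a mechanism. With equal assumed differences and zero within-group correlation, the false-positive rate is about 5–7% for d up to 0.5, 16% at 0.8, 29% at 1.0 and 48% at 1.2. It is near nominal when either difference is small.

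A reader might infer that Hypothesis 2 guarantees a significant Hypothesis 1. The documents do not support that: they give no group differences, and even at d = 1.0 on both variables the pooled test would miss significance about 71% of the time (100% − 29%). Nor does the article claim that the two hypotheses are independent evidence.

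The matter affects one part of a secondary aim and not the relapse algorithm. It should be fixed before analysis.

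**What to change.** Make the main test of Hypothesis 1 the correlation adjusted for diagnosis in all 50 participants: regress molecular amplitude on Relative Amplitude plus group and test the Relative Amplitude coefficient. Report the BD-only, control-only and unadjusted pooled estimates beside it, and state that the pooled estimate alone will not be read as mechanistic evidence.

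The change takes a sentence or two in the Study 2 protocol or analysis plan and one degree of freedom (47 instead of 48). It needs no new data and costs about one percentage point of power at a within-group correlation of 0.4.
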